### **Data Collection**

#### **Scales/Measures**

The following scales will be administered to all participants at baseline, before randomization and separate from other scales: (1) Socio-demographic questionnaire to identify potential confounding factors, during analysis; (2) Global Appraisal of Individual Needs- Short Screener (GAIN-SS) to screen participants as having severe behavioural health disorders, and to measure behavioural health change over study time. The following scales will be administered to all participants at baseline, at the 3 month mark and 6 month mark: (3) General Help Seeking Questionnaire to measure intentions to seek help from different sources and for different problems; (4) Actual Help Seeking Questionnaire to measure past help-seeking experiences; (5) Attitudes Towards Seeking Professional

Psychological Help –Short Form to measure participants process of seeking professional help; (6) Self-Stigma of Seeking Help Scale to measure change in participants self-stigma of seeking psychological help; and (7) Youth Efficacy/Empowerment Scale to measure change in participants empowerment and efficacy when consuming mental health services.

A 6-week reminder and an 18-week reminder will be sent to participants to support their engagement in the study over the 6-month period.

An end-of study usability survey will be administered to participants in the intervention arm at the 6-month mark of the study. This survey measures usefulness, satisfaction and ease of use of the Thought Spot application. The purpose of the survey is to explore factors related to app acceptance, feasibility and performance that may affect help-seeking intentions, behaviours and attitudes of study participants. The survey also asks a short series of demographic questions to identify the respondent's place of residence (downtown Toronto, GTA or other city) because place of residence is a factor in usability. Finally, the survey asks about intentions for future use, whether the respondent would recommend the app to a friend and includes open-ended questions for additional feedback.

#### **Digital data collection**

The monitoring of participant data is valuable to the validation of the Thought Spot platform. Digital data will be used to expand on the self-report data collected from participants through the various scales and measures listed above. Usage metrics outlining the intensity of use, usage of content, and methods of accessing app data will be calculated and analyzed. Simple descriptive statistics will also be used to report the time spent on specific app features; number of times the app is used in a day; what times in the day features are being used; and added spots, journal entries, and reviews. This data will be collected from individual, di-identified user accounts. Some of the digital data will also be used to inform app enhancements and plans for development.

#### **End-of-study qualitative interviews**

A purposeful sample of 15-20 participants in the intervention group who completed the usability survey will be invited to participate in a 30-60 minute in-person or telephone interview to better understand enablers and barriers to using Thought Spot and its impact on help-seeking intentions, help-seeking behaviours and attitudes, health literacy, self-efficacy and empowerment.

The interviews will be conducted in a semi-structured manner with a set of predetermined open-ended questions and probing questions between interviewer and participant. Interviews will be audio recorded and transcribed. The transcripts will be codified and analyzed for themes related to enablers and barriers to use, app acceptance, feasibility, performance, as well as the impact of Thought Spot on help-seeking intentions, health seeking behaviours and attitudes, health literacy, self-efficacy and empowerment.

#### **Withdrawal criteria**

Participants are free to leave the study at any time. If participants decide to stop participating at any point during the study, they may also decide whether they want any of the information that they have

contributed up to that point to be removed or if they will allow us to use that information towards our analysis. Participants will be compensated for the number of completed surveys.

### **Safety Considerations and Risks**

We are aware that some students may also utilize Thought Spot for crisis support. Access to appropriate mental health crisis support will be identified for each university or college recruitment site. A prominent crisis-redirect “help” feature is built into the app for students to use to immediately connect to crisis resources and help lines. Key members of the research team will be able to provide emergent clinical input or direction, should the need arise. These members of the research team will also provide direction and training to ensure appropriate, meaningful, and effective engagement with transition-aged youth.

In addition, students may have concerns or feel vulnerable that personal information, which they enter into the app may be made public through the research process. Students will be provided information through the consent form about what kinds of digital user-information will be gathered from the app for the research.

Finally, students who are in the control arm of the study may feel disappointed or upset that they were not selected to access the app and/or they may have been joining the study due to the need for support in identifying or accessing mental health services or wellness resources. A resource pamphlet will be made available to all students in the control group with information about crisis support services and other mental health and wellness resources across the GTA.

### **Adequacy of protection against risks**

We will be engaging vulnerable individuals in this process, and protocols will be put in place to monitor and respond to participants’ needs at various stages in the study. We anticipate that these measures will be adequate to protecting participants for issues that arise.

- 1) Access to appropriate mental health crisis support will be identified for each university or college recruitment site, and information regarding services will be provided to all participants. Information regarding these crisis support services will be provided to all participants. A prominent crisis-redirect “help” feature is built into the app for students to use to immediately connect them to crisis resource and help lines.
- 2) Key members of the research team will be able to provide emergent clinical input or direction, should the need arise. These members of the research team will also provide direction and training to ensure appropriate, meaningful, and effective engagement with youth, especially vulnerable youth.
- 3) Participants will be provided with information about what kinds of digital user-information will be gathered from the app for the research. This data will only consist of aggregated (group-level) data about usage trends, and therefore the data will be anonymous and will not consist of any information tied to specific individuals.
- 4) A resource pamphlet will be made available to all students in the control group with information about crisis support services and other mental health and wellness resources.

- 5) Being audio-recorded may feel awkward or embarrassing for some participants. It is disclosed to the participants on the consent form for the end-of-study interviews that their interviews will be audio-recorded. If they are uncomfortable, they can choose not to participate in this aspect of the study. If they start to feel uncomfortable during the interview, we will choose to terminate the interview for the well-being of the participant.

### **Potential Benefits**

There is no guarantee that participants will benefit in any way from taking part in this study. Participants who are in the intervention arm of the study may experience enhanced help-seeking efficacy around mental health and wellness resources and services through the use of this interactive, dynamic, updatable digital engagement platform. Individuals in the control arm may sustain some of the similar gains, simply by signing up for a study about mental health and wellness and being provided a resource pamphlet with listings of mental health and wellness services. This project harnesses the knowledge of the students themselves, to deliver a sustainable approach to activate youth to have productive interactions with health care systems.

The investigators responsible for this study or the CAMH are not conducting this study to receive commercial benefit. However, if this research produces financial returns from a commercialization of the results in the future, participants will not receive any benefit from these returns.

### **Safety Monitoring**

Study investigators will meet monthly to review data confidentiality, adherence to protocol design, recruitment, and participant complaints. They will determine whether there has been any change in the benefit-to-risk ratio of the study. If an adverse event occurs, it will be reported to the research ethics board. If an unexpected adverse event occurs, the investigators will re-assess the risk/benefit ratio of the study; if deemed necessary, they will submit any modifications to all research ethics boards for approval. At the time of REB annual renewal, the PI will submit to the REB the information about the frequency of the monitoring for adverse events and complaints, the dates that meetings took place, a summary of the cumulative adverse events and complaints, external factors or other relevant information that might have an impact on the safety or ethics of the study, final conclusion regarding changes to the anticipated risk/benefit ratio to study participation, and final recommendations related to the continuation, change, or termination of the study.

### **Confidentiality**

#### **REDCap**

Data entered in surveys through REDCap, the platform used to house the online surveys can only be accessed with a password known to key research staff working on the project. Only the investigators and key research staff supported by this project will have access to participants' identities and linked research materials. All data collected through REDCap will be stored in various relational database tables through the use of foreign keys and indexes. This is within a single MySQL database, which is an open source RDBMS (relational database management system). The front end of REDCap is written in PHP, which is widely used, robust, open source scripting language. Setting up the web server and database server and securing the communication of the servers to each other and to the end-user are the responsibilities of the partner institution that is installing REDCap, and thus must be completed prior to installing REDCap. The institution installing REDCap will store all data captured in REDCap on its own

servers. Thus, all project data is stored and hosted there at the local institution, and no project data is ever transmitted at any time by REDCap from that institution to another institution or organization.

To help protect and secure the data stored in REDCap's back end database, the software application employs various methods to protect against malicious users who may attempt to identify and exploit any security vulnerabilities in the system. Such methods will be described here in technical detail. In REDCap, all incoming data gets intentionally filtered, and sanitized. This includes all data submitted in an HTTP Post request and all query string data found in every URL while accessing REDCap, among other modes through which user-defined data gets submitted in the application. Server environment variables that are vulnerable to forgery by users are also checked and sanitized. All user submitted data is properly filtered for any possibly harmful markup tags.

### **Digital Data**

All digital data will be stored on a secured server that is password protected at CAMH and that is part of a system and facility designed to ensure the privacy of this information. A list linking the unique identifier, e-mail login for Thought Spot, with the participant's name and contact information will be stored separately in a password protected file on a password protected CAMH computer that is on a secured server.

### **Qualitative Interview Data**

Confidentiality of all collected data is of primary concern and every effort will be made to ensure data management respects the privacy and confidentiality of participants. The data collected regarding the participants will not be shared with anyone except with the participant's consent or as required by law. Identifiable information such as the participant's name or any other identifying information will be removed from the transcripts. Audio-recordings of interviews will be destroyed after analysis.

### **Data Storage**

All data including paper copies, audio recordings, and transcripts will be securely stored in a locked filing cabinet in a locked office at the Centre for Addiction and Mental Health, [name]. All hard copy materials such as participant consent forms will be securely stored in a locked filing cabinet in a locked office at the Centre for Addiction and Mental Health, [name]. All data pertaining to a participant's involvement in this study will only be accessible to the research team. The data for this research study will be retained for 25 years. During this time information will be stored in a locked filing cabinet and a password protected computer in a secure room at the Centre for Addiction and Mental Health, [name]. After this time, paper information will be shredded and computerized data will be purged and deleted.

### **Reporting**

Participants will not be identified by name in any publication of research results. Results will be published as group data without the use of characteristics that would identify individual participants.

### **Analysis**

#### **Power Analysis**

The outcome considered for our power calculation is the average of the GHSQ scale for the formal sources, although similar effect and sample sizes are expected for the informal sources. To determine the sample size required to test the primary hypothesis that the Thought Spot intervention will cause a greater change in help-seeking intentions than usual care, a series of Monte Carlo simulations were

carried out (with 10,000 replications under each test scenario) using SAS System 9.4 for Windows [35]. These simulations assume that the primary hypothesis will be tested using mixed-effect models to account for the longitudinal design, and linear contrasts between time and arm to compare the changes from baseline in both arms. We assume that the test will be 2 tailed and with a critical Cronbach alpha level of 0.05. In order to simulate the data, the means, standard deviations, and within-subject associations are assumed to follow published data that have used similar study designs [36,37]. Based on previous research using the GHSQ [38], a small effect size, equivalent to a Cohen's d of 0.25, was considered (ie, an average change in the GHSQ of 0.41, which is equivalent to a change of 15%), within-subject correlation of 0.6, attrition rate of 40%, and power of 80%. Based on these simulations and specifications, a sample of 236 subjects per arm at baseline is required, which amounts to 472 subjects in total. If 40% attrition is applied to this initial sample, we will be left with 142 subjects per arm (283 in total) after 6 months, at the conclusion of the study.

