**Sample size**

To determine the sample size required to test the primary hypothesis that the Thought Spot intervention will cause a greater change in help seeking intentions compared to usual care, as measured by the difference in formal help seeking intentions from 6 months to baseline, a series of Monte Carlo simulations were carried out (with 10000 replications under each test scenario) using SAS System for Windows v.9.4 (SAS Institute Inc. Cary, NC). These simulations assume that the primary hypothesis will be tested using Mixed Effect Models to account for the longitudinal design and contrasts using time and arm to compare the changes from baseline in both arms. We assume that the test will be two tailed and with critical alpha level of 0.05. In order to simulate the data, means and standard deviation, as well as within subject association are assumed to follow published data that used similar study design. A small effect size, equivalent to a Cohen's d of 0.25, was considered (i.e., an average change in the Help-Seeking Scale of 0.41 - which is a change of 15%), within subject correlation of 0.6, attrition rate of 40% and power of 80%. Based on these simulations and specifications, a sample of 236 subjects per arm before attrition should be used.

To prevent dropping below the 60% response rate required, we will examine our response rates for the final T2 surveys (6 month survey) when the first block of approximately 50-100 participants completes the T2 survey at the 6-month mark of the study. We are proposing to recruit an additional 50 participants if we drop below a 65% response rate at that point. The rationale for this decision is to maintain the power for the analysis in this study.

The participants in the intervention arm will be invited to a usability survey at the 6-month mark which measures usefulness, satisfaction and ease of use of the Thought Spot application. The sample for this survey is limited to the intervention arm because only these participants had access to the Thought Spot application.

A purposeful sample of 15-20 participants who completed the usability survey will be invited to participate in a 30 minute in-person or telephone qualitative interview to better understand enablers and barriers to using Thought Spot and its impact on help-seeking intentions, health literacy, self-efficacy and empowerment. The purposeful sampling criteria follows:

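### With 236 per arm and 40% attrition, the protocol's own inputs give about 70% power for the primary contrast, not the stated 80%

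*Protocol*

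**What the plan says.** The Sample size and Power Analysis sections of the protocol describe one Monte Carlo exercise in SAS and give the same inputs.

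- **Test:** "We assume that the test will be two tailed and with critical alpha level of 0.05". Power Analysis also says two-tailed, and its slip about Cronbach alpha is corrected in the Statistical Analysis Plan Change Log.
- **Effect:** "a small effect size, equivalent to a Cohen's d of 0.25, was considered", described as "an average change in the GHSQ of 0.41, which is equivalent to a change of 15" per cent.
- **Correlation, attrition, power:** "within-subject correlation of 0.6, attrition rate of 40%, and power of 80" per cent.
- **Numbers:** "attrition rate of 40%, and power of 80%. Based on these simulations and specifications, a sample of 236 subjects per arm" at baseline, after which "we will be left with 142 subjects per arm (283 in total) after 6 months".

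The tested quantity is fixed too. The Statistical Analysis Plan section specifies a mixed model fitted by maximum likelihood to all available data. Group, time point and their interaction are predictors, and the comparison is a contrast on change from baseline to the last visit. A completers-only fit is a sensitivity analysis. The Change Log confirms that the contrast in the power calculation is the same as the primary test.

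Sample size adds a safeguard: "We are proposing to recruit an additional 50 participants if we drop below a 65% response rate at that point". Its stated reason is to maintain power.

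**The concern.** A baseline-to-6-month contrast depends mainly on those still responding at 6 months, about 142 per arm. With a correlation of 0.6, an effect of 0.25 SD and a two-sided 5% test, that number looks too small for 80% power.

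What is at stake is how the primary result is read. If true power is about 70%, the chance of missing the effect the trial was designed for is about 30%, not 20%. The Change Log reports no evidence of an effect on the primary outcome, and the sex- and gender-based analysis was not done for that reason. A reader who sets that null result against a claimed 80% will take it as stronger evidence of no effect than the design supports.

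**Working it through.** **Inputs.** From the protocol: n = 236 per arm, 40% missing at 6 months, d = 0.25, correlation 0.6, two-sided alpha 0.05, visits at 0, 3 and 6 months. Implied SD: 0.41 / 0.25 = 1.64 points. Assumed here, because the protocol does not state them: compound symmetry, equal SDs at all visits, d standardised by the raw-score SD, no gain from covariates, and 3-month missingness anywhere from 0% to 40%.

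**The plan's own figures.** 236 × 0.6 = 141.6, or 142 per arm, and 472 × 0.6 = 283.2, or 283 in total. The retention arithmetic reproduces; the 80% does not, as follows.

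**Completers only (the sensitivity analysis).** Variance of change = 2(1 − 0.6) = 0.80 SD². SE = √(2 × 0.80 / 141.6) = 0.1063. z = 0.25 / 0.1063 = 2.352. Power = Φ(2.352 − 1.960) = 65%.

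**Planned mixed model.** Maximum likelihood also uses the visits of those who later drop out. Under compound symmetry 0.6:

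- Month 6 regressed on baseline and month 3 has weights 0.6 / 1.6 = 0.375 each and residual variance 1 − 2 × 0.375 × 0.6 = 0.55.
- Month 3 regressed on baseline has residual variance 1 − 0.36 = 0.64, which contributes 0.375² × 0.64 = 0.09.
- The net weight on baseline is 0.375 + 0.375 × 0.6 − 1 = −0.4, which contributes 0.16.

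Variance of the group contrast, in SD² units: V = 2 × (0.55/n6 + 0.09/n3 + 0.16/n0). As a check, without dropout the three terms sum to 0.80, the change-score variance.

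With n0 = 236 and n6 = 141.6:

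| Missing at 3 months | n3 | V | SE | z | Power, two-sided 5% | Power, one-sided 5% |
|---|---|---|---|---|---|---|
| 0% | 236 | 0.00989 | 0.0994 | 2.514 | 71.0% | 80.8% |
| 20% | 188.8 | 0.01008 | 0.1004 | 2.490 | 70.2% | 80.1% |
| 40% | 141.6 | 0.01040 | 0.1020 | 2.452 | 68.9% | 79.0% |

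A simulation of the 20% row with 10,000 replicates gave power 0.705 and type I error 0.052.

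**Size needed for 80%.** n = 236 × (2.802 / z)², where 2.802 = 1.960 + 0.842. This gives about 293, 299 and 308 per arm for the three rows.

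**Effect detectable with 80% power at 236 per arm.** 2.802 × SE = 0.279 to 0.286 SD. Times 1.64, that is 0.46 to 0.47 points.

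**With the 50 extra participants.** 261 per arm at 60% retention multiplies z by √(261/236) = 1.052, giving 2.58 to 2.64 and power 73% to 75%.

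**A favourable correlation pattern.** Take 0.6 between baseline and month 6, 0.775 between adjacent visits, and all dropout after month 3. The residual variance falls to 0.399 and the remaining term, carried by all 236, is 0.401. V = 2 × (0.399/141.6 + 0.401/236) = 0.00904, z = 2.63, power 75%.

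**Simulation noise.** At 80% power and 10,000 replications the standard error is √(0.8 × 0.2 / 10,000) = 0.4 percentage points. That cannot explain a gap of about 10 points.

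**The case against.** The strongest reply is that the published inputs do not fix the power completely. The protocol takes its means, SDs and within-subject associations from published data, and neither the simulation code nor the full covariance matrix is shown. A common correlation of 0.68 to 0.70 instead of 0.6 would give about 78% to 82%. A model with linear time and equal baseline means would give 76% to 82%. A baseline SD 15% below the follow-up SD would give 72% to 75%.

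This stands as a reason to state the assumptions and to say about 70% rather than give a falsely exact figure. It does not rescue the 80%. A correlation of 0.68 or more departs from the stated 0.6, and the linear-time model is not the one specified. Uncertainty also runs the other way: an autoregressive pattern with 0.6 between adjacent visits gives 51% to 55%.

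A reader might go further in three directions that the documents do not support.

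- **That the simulation was run one-sided.** A one-sided 5% test does give 79% to 81%, but the protocol states a two-sided test throughout. Without the code this is conjecture, and it is not the only route to about 80%.
- **That power is 65%, with a 35% risk of missing the effect.** That figure belongs to the completers-only sensitivity analysis, not to the primary test.
- **That the top-up rule is faulty.** It was written to guard the 60% response rate, not to repair the sample size. With 522 enrolled, 283 completers are kept down to 283/522 = 54% retention, which is a margin beyond the planned 60%. There is no contradiction; the extra 50 simply do not bring power to 80%.

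**Conclusion.** The 80% is wrong as written. For the stated two-sided contrast in the planned model, 236 per arm with 40% attrition gives about 70% power (69% to 71%). This rests on compound symmetry at 0.6, equal SDs and no covariate gain; under these, the timing of dropout hardly matters. If adjacent visits correlate more highly, timing does matter, and late dropout takes power to about 75%, still short of 80%. The shortfall is about 10 points of power, or a detectable effect about 0.05 to 0.06 points larger than the 0.41 claimed.

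Type I error, the choice of contrast, the model and the treatment estimate are unaffected. The point does not undermine the primary analysis; it limits how firmly a null result can be read as absence of the design effect.

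**What to change.** Keep the sample size. In both the Sample size and Power Analysis sections:

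- State that 236 per arm with 40% attrition gives about 70% power for 0.41 points (0.25 SD), and 80% power for about 0.46 to 0.47 points (0.28 to 0.29 SD).
- List the assumptions behind the figure: the correlation between each pair of visits, the SD at each visit, and the share missing at 3 and at 6 months. If the simulation used values or a model that do give 80%, show them there.
- Interpret a null primary result against about 70% power and alongside its confidence interval.

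The top-up rule needs no change. The cost is a few sentences and a less favourable power statement; no participants, visits or analyses are added.
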